## Abstract

**Background:**

The antral region of pulmonary veins (PV)s seems to play a key role in a strategy aimed at preventing atrial fibrillation (AF) recurrence. Particularly, low‐voltage activity in tissue such as the PV antra and residual potential within the antral scar likely represent vulnerabilities in antral lesion sets, and ablation of these targets seems to improve freedom from AF. The aim of this study is to validate a structured application of an approach that includes the complete abolition of any antral potential achieving electrical quiescence in antral regions.

**Methods:**

The improveD procEdural workfLow for cathETEr ablation of paroxysmal AF with high density mapping system and advanced technology (DELETE AF) study is a prospective, single‐arm, international post‐market cohort study designed to demonstrate a low rate of clinical atrial arrhythmias recurrence with an improved procedural workflow for catheter ablation of paroxysmal AF, using the most advanced point‐by‐point RF ablation technology in a multicenter setting. About 300 consecutive patients with standard indications for AF ablation will be enrolled in this study. Post‐ablation, all patients will be monitored with ambulatory event monitoring, starting within 30 days post‐ablation to proactively detect and manage any recurrences within the 90‐day blanking period, as well as Holter monitoring at 3, 6, 9, and 12 months post‐ablation. Healthcare resource utilization, clinical data, complications, patients' medical complaints related to the ablation procedure and patient's reported outcome measures will be prospectively traced and evaluated.

**Discussion:**

The DELETE AF trial will provide additional knowledge on long‐term outcome following a structured ablation workflow, with high density mapping, advanced algorithms and local impedance technology, in an international multicentric fashion. DELETE AF is registered at ClinicalTrials.gov (NCT05005143).

## INTRODUCTION

1

The standard approach to the treatment of paroxysmal atrial fibrillation (PAF) is pulmonary vein isolation (PVI).^1^, ^2^ Complete electrical isolation of the PVs with documented entrance and/or exit block has better rhythm outcomes than incomplete isolation;^3^ however, long‐term atrial arrhythmia‐free survival is still unsatisfactory^4^ and a high incidence of PV reconnection has been reported in patients with clinical recurrences of AF.^2^, ^5^, ^6^ The antral region of PVs seems to play a key role in a strategy aimed at preventing AF recurrence.^7^ Particularly, low‐voltage activity in tissues such as the PV antra and residual potential within the antral scar (RAP) likely represent vulnerabilities in antral lesion sets, and ablation of these targets seems to improve freedom from AF as reported by Segerson et al.^8^ in a single‐center fashion by using the Rhythmia^TM^ HDx mapping system (Rhythmia^TM^; Boston Scientific) and standard radiofrequency (RF) ablation catheters. These results were driven by performing high‐density mapping of PV antra after traditional encirclement lesions through a structured workflow approach. Broader clinical application of this technique and recreation of these high AF efficacy rates await confirmation by other investigators and validation with a prospective, multicenter large clinical study, also by using the most advanced mapping and ablative technologies. The aim of the improveD procEdural workfLow for cathETEr ablation of PAF with high‐density mapping system and advanced technology (DELETE AF) study is to fill this clinical evidence gap.

## METHODS

2

The study complied with the Declaration of Helsinki, the locally appointed ethics committee approved the research protocol, and informed consent will be obtained from all patients. This trial is registered at clinicaltrials. gov (NCT05005143).

### Study design

2.1

DELETE AF is a prospective, single‐arm, international postmarket cohort study designed to demonstrate a low rate of clinical atrial arrhythmias recurrence with an improved procedural workflow for catheter ablation of PAF, using the most advanced point‐by‐point RF ablation technology in a multicenter setting. The study flowchart is depicted in Figure 1. The study is approved by the Institutional Review Boards of the participating centers. The trial will be conducted in accordance with the “Declaration of Helsinki” (1964 and later amendments).

**Figure 1 clc23806-fig-0001:**
[figure not shown]
DELETE AF study flowchart. 3D, three dimensional; DELETE AF, improveD procEdural workfLow for cathETEr ablation of paroxysmal atrial fibrillation; ECG, electrocardiogram; QOL, quality of life

### Patient enrollment

2.2

Enrollment will start in January 2022 and are planned to end in December 2022. Up to 300 consecutive patients are planned to be enrolled at 10 European centers. All patients will undergo a baseline screening examination, to verify eligibility criteria. After signing an informed consent form, consecutive patients undergoing AF ablation will be prospectively enrolled. The patient's clinical data and procedural management information will be collected.

### Patient population

2.3

Subjects enrolled in the DELETE AF study will be clinically indicated for a standard‐of‐care endocardial catheter‐based ablation procedure under the Rhythmia^TM^ mapping system guidance for the treatment of AF and meet the study inclusion/exclusion criteria as outlined in Table 1.

**Table 1 clc23806-tbl-0001:** Inclusion and exclusion criteria for enrollment in the DELETE AF study

Inclusion criteria: a) History of recurrent symptomatic PAF with ≥1 episode reported and documented within the 365 days before enrollment b) Indication to an ablation procedure with 3D high‐density mapping system according to current international and local guidelines c) Willingness and ability to provide informed consent, participating in all testing at an approved clinical investigational center d) Age ≥18 years or above, and of legal age to give informed consent specific to state and national law
Exclusion criteria: a) Persistent or long‐standing persistent AF b) Participation in another clinical study that may have an impact on the study endpoints c) Unwillingness or inability to sign an authorization to use and disclose health information or an Informed Consent form d) Unwillingness or inability to complete follow‐up visits and examination for the duration of the study at the center e) Life expectancy ≤12 months f) Previous cardiac ablation within 90 days before enrollment g) Unrecovered/unresolved adverse events from any previous invasive procedure h) Women of childbearing potential who are, or plan to become, pregnant during the time of study i) Left atrial size >60 mm diameter on echocardiogram j) Left atrial thrombus in preprocedure imaging within 4 weeks of the ablation procedure k) AF secondary to electrolyte imbalance, thyroid disease, or reversible noncardiac cause l) History of prior surgical ablation for AF or atypical atrial flutter, including MAZE or mini‐MAZE

Abbreviations: DELETE AF, improveD procEdural workfLow for cathETEr ablation of paroxysmal atrial fibrillation; PAF, paroxysmal atrial fibrillation.

### Ablation treatment

2.4

All procedures will be performed under conscious sedation or general anesthesia according to centers' preference. All patients will be treated according to a prespecified structured workflow followed by each center. After single or double transseptal punctures under fluoroscopic guidance, intravenous unfractionated heparin boluses will be administered, to maintain an activated clotting time of >300 seconds. The basket mapping catheter (Orion^TM^; Boston Scientific) and the ablation catheter (IntellaNav MiFi OI^TM^ or IntellaNav StablePoint OI^TM^; Boston Scientific) will be then inserted through steerable sheaths. The Orion^TM^ catheter will be used in combination with the Rhythmia^TM^ HDx mapping system to create a three‐dimensional electroanatomical voltage and activation map of the left atrium. The ablation target in all patients will be PVI and the achievement of complete electrical quiescence within the antral region. PVI will be performed by means of RF energy in a point‐by‐point ablation pattern by the open‐irrigated ablation catheter. Point‐by‐point RF delivery will be performed in such a way as to create contiguous ablation spots encircling the PVs. The maximal interlesion distance between two neighboring lesions will be set ≤6 mm. Ablation will be guided by the magnitude and time course of the impedance drop during RF delivery.^9^, ^10^, ^11^ Power settings will be set at the individual operator's discretion, within the range of 30–50 W, depending on the left atrial segment considered.

The endpoint of ablation is PVI, as assessed on the basis of entry and exit block by means of the 64‐pole Orion^TM^ catheter placed sequentially in each of the PVs, and the achievement of complete electrical quiescence within the antral region. The Lumipoint^TM^ map analysis tool, which automatically identifies fragmented potentials and continuous activation, will be used sequentially on each PV component, to assess the presence of PV gaps (PVGs) and RAPs and to characterize electrical propagation. After identification of an atrial site with PVG or RAP by means of the Lumipoint^TM^ software, both the voltage map and the standard activation/propagation map will be investigated to check for agreement. Regarding the ablation strategy, each residual PVG will be first targeted to guarantee contiguity in the lesion set. Second, after confirmation of bidirectional isolation, when any low‐voltage propagation is suspected within the region of previous antral ablation and are confirmed by information from the Lumipoint^TM^ tool and by consistency with regional activation timing,^8^ additional focal ablations will be performed. These ablations will be then reassessed by means of repeat Lumipoint^TM^ and voltage and propagation mapping until electrical quiescence will be achieved. A detailed description of the procedural workflow is depicted in Figure 2. Example of the ablation workflow, identification of PVGs and residual RAPs detected through Lumipoint^TM^ according to the procedural workflow and demonstration of PVI, and complete electrical quiescence at the end of the ablation are reported in Figure 3A–C.

**Figure 2 clc23806-fig-0002:**
[figure not shown]
DELETE AF procedural workflow. DELETE AF, improveD procEdural workfLow for cathETEr ablation of paroxysmal atrial fibrillation; PV, pulmonary vein; RF, radiofrequency

**Figure 3 clc23806-fig-0003:**
[figure not shown]
(A) The DELETE AF ablation protocol. Posterior view (left panel) and anterior view (right panel), using the Rhythmia^TM^ mapping system. Point‐by‐point RF delivery created contiguous ablation spots encircling the PVs. The maximal interlesion distance between two neighboring lesions was set ≤6 mm and was automatically measured through the Autotag^TM^ software. Power settings are set at the individual operator's discretion, within the range of 30–50 W, depending on the left atrial segment considered. In this example, power setting was 45 W at the posterior site (blue dots) and 50 W at anterior sites (red dots). (B) Examples of PVG (upper panel) and residual RAP (lower panel) detected through Lumipoint^TM^ tool according to the procedural workflow. (C) After the antral lesion set was delivered, the Orion^TM^ catheter was engaged in the PVs to assess circumferential luminal electrical activity and the Lumipoint^TM^ tool was used sequentially on each PV component, to assess the presence of PVGs and RAPs and to characterize electrical propagation. In this example, antral isolation and electrical quiet were demonstrated in all the PVs after PV isolation and antral ablation. DELETE AF, improveD procEdural workfLow for cathETEr ablation of paroxysmal atrial fibrillation; PV, pulmonary vein; PVG, PV gap; RAP, residual potential within the antral scar; RF, radiofrequency

### Follow‐up evaluation program

2.5

Post ablation, all patients will be monitored with ambulatory event monitoring, starting within 30 days post ablation to proactively detect and manage any recurrences within the 90‐day blanking period, as well as Holter monitoring at 3, 6, 9, and 12 months post ablation. Additional electrocardiogram (ECG) monitoring will be performed as indicated by patient symptoms. At each visit, a medical history will be performed to ascertain if there has been a change in medications or of cardiac status (Figure 1). Healthcare resource utilization (hospital or emergency room access, planned and/or unplanned follow‐up visits, diagnostic examinations), clinical data, complications, and patients' medical complaints related to the ablation procedure will be prospectively traced. Patient‐reported outcomes questionnaires will be completed at each study visit to measure the quality of life: the EQ‐5D‐5L, the Specific Symptom Scale Score,^12^, ^13^, ^14^ and the EHRA Score of AF‐related Symptoms.

### Study hypotheses

2.6

This prospective cohort study has been specifically designed to demonstrate a low rate of clinical atrial arrhythmia recurrence with an improved procedural PVI workflow^8^ for catheter ablation of PAF in a multicenter setting, using the most advanced point‐by‐point technology versus recent literature reference on ablation of PAF.^15^, ^16^, ^17^, ^18^

Apart from its primary purpose, the study will evaluate the association between the occurrence of atrial arrhythmias and baseline patient's characteristics (clinical history and drug therapy) or procedural data (post hoc voltage and activation maps analysis), will estimate costs associated with the use of health care resources, rate of the adverse events associated with the primary ablation procedure, and overall procedure time. Moreover, periprocedural factors (e.g., periprocedural anticoagulation management or total fluoroscopy time and contrast medium utilization) associated with the 12‐month outcome and the acute procedural success will be investigated.

### Primary endpoint

2.7

The primary endpoint of the study is the rate of success at the medium‐term follow‐up after PVI in consecutive patients undergoing AF ablation. Specifically, the primary outcome measure of this study is the percentage of patients with documented arrhythmias after 12 months from the procedure. Arrhythmias are defined as any AF, atrial flutter, or atrial tachycardia episode, continuously for >30 seconds, as recorded by any postablation ECG modality. Arrhythmia recurrences within the first 3 months (blanking period) are classified as early recurrences and will not be considered a procedural failure.

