### Secondary endpoints

2.8

Nine secondary endpoints will be evaluated. Specifically:
1.Acute procedural success of AF ablation. The acute success of the AF ablation is verified by the completion of the necessary ablation application(s), the validation of ablation through appropriate technique(s), and, when applicable, the termination of the primary arrhythmia.2.Recurrence of AF‐only arrhythmia after 12 months from the procedure.3.Occurrence of all kinds of atrial arrhythmias. A sustained atrial flutter/atrial tachycardia is defined as >30 seconds arrhythmia occurrence as recorded on a monitoring device.4.Percentage of patients free from any clinical atrial arrhythmias according to procedure type (de novo vs. redo ablation).5.Association between baseline patient's characteristics and electroanatomical variables derived from the evaluation of voltage and activation maps and arrhythmias' occurrence at 12 months.6.Repeated ablation procedures (after the index procedure). The number of ablation procedures for the treatment of the primary arrhythmia after the index procedure.7.Procedure‐related adverse events: number, type, and rate of the adverse events that occur during the procedure and during 12 months follow‐up.8.Patient‐reported outcomes: EQ‐5D‐5L, Specific Symptom Scale Score, and EHRA Score of AF‐related Symptoms.9.Health Economic units: resource consumption and the associated costs in terms of ablation procedures, follow‐up, management of complications, and health care resources utilization.

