### Sample size justification

2.11

The DELETE AF study is designed to be observational and comparisons to published data will be done in a post hoc fashion. The sample size requirements for this study are intended to provide adequate power for the analysis of the primary objective.

Assumptions and their rationale:
75% Atrial arrhythmias recurrence‐free rate (performance goal set according to published data).^15^, ^16^, ^17^, ^18^
Both large, multicenter randomized clinical trials^16^, ^17^ and pooled results^15^ that compared the two most common ablation approaches (RF ablation and cryoablation) demonstrated that the efficacy of cryoablation was noninferior to RF ablation at 12 months. In a very recent metanalysis,^18^ the most advanced RF ablation technology was associated with higher freedom from AF/atrial tachycardia at 12 months, compared with conventional ablation catheters in paroxysmal AF patients (75.6% vs. 64.7%; *p* = .015).85% Expected performance in the study groupIn a single‐centre study, Segerson et al.^8^ demonstrated a 90.7% recurrence‐free rate in patients who underwent high‐density mapping (HDM)‐guided PVI and subsequent mapping and ablation of concealed low‐voltage signals through a structured workflow vs. a 73.9% recurrence‐free rate in the group of historical controls who underwent traditional PVI alone. Considering the multicenter setting of the present study, the variable number, and the experience of the operators performing ablation procedures, we set this cutoff to 85%.Actual power 90% (*β* level set at 0.1)The proportion of patients free from any clinical atrial arrhythmias (primary objective) will be measured in the subgroup of “Treatment” subjects. The number of “Attempt” patients (subjects the procedure is not performed according to the prespecified workflow) is not known. Therefore, the enrollment phase will continue until 200 patients are included in the “Treatment” group (190 patients + 5%, i.e., maximum expected attrition rate during follow‐up), up to a maximum of 300 subjects.

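### The primary endpoint applies one continuous >30 s threshold to whichever ECG modality is used and makes no provision for tracings of 30 s or less, so a recurrence seen only on a short symptom-driven ECG scores as a success.

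*Protocol article*

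**What the plan says.** Section 2.7 of the protocol article (Primary endpoint) gives one definition of the failure event: AF, flutter or atrial tachycardia lasting "continuously for >30 seconds, as recorded by any postablation ECG modality". The first three months are excluded: "Arrhythmia recurrences within the first 3 months (blanking period) are classified as early recurrences and will not be considered a procedural failure".

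Section 2.5 (Follow-up evaluation program) describes how rhythm is observed. Ambulatory event monitoring starts within 30 days and is described in terms of recurrences in the blanking period; when it ends is not stated. Scheduled recording is then by Holter: "as well as Holter monitoring at 3, 6, 9, and 12 months post ablation". Between those points, "Additional electrocardiogram (ECG) monitoring will be performed as indicated by patient symptoms". The type and length of those symptom-driven recordings are not given.

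Section 2.8, secondary endpoint 3, repeats the duration but words the source differently: "A sustained atrial flutter/atrial tachycardia is defined as >30 seconds arrhythmia occurrence as recorded on a monitoring device".

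Section 2.11 compares the recurrence-free proportion with 75%, described as a "performance goal set according to published data".

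**The concern.** The definition admits every ECG modality as a source of evidence, then sets a duration that a short tracing cannot reach even when arrhythmia fills it from start to end. A threshold of >30 s is reasonable for Holter, event recorders and other long recordings. The difficulty is that it extends without qualification to recordings no longer than the threshold.

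Take a patient who attends with palpitations in month 5. A short ECG shows AF throughout, sinus rhythm returns before any longer recording is made, and the Holters at 6, 9 and 12 months are clean. Under 2.7 as written this patient is free of recurrence. Yet sections 2.1 and 2.6 state the aim as a low rate of clinical arrhythmia recurrence, and a symptomatic, ECG-documented episode is close to the centre of that aim.

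The study has one arm and a fixed goal, so there is no concurrent control group in which such missed events could cancel. Read literally, the gap can only raise the success proportion.

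**Working it through.** **1. The text, side by side.**

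- 2.7: duration >30 s, continuous; source: any post-ablation ECG modality; no exception for short recordings.
- 2.5: Holter at four fixed times, plus ECG monitoring prompted by symptoms, of unstated type and length.
- 2.8, endpoint 3: duration >30 s for flutter and tachycardia; source: a monitoring device.

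None of these counts an arrhythmia that fills a whole short tracing, and none makes a symptomatic documented arrhythmia a failure whatever its recorded length. The 10 s length of a standard 12-lead ECG is an assumption, but the reasoning holds for any tracing of 30 s or less.

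**2. Inputs for the size.** From 2.11: goal p0 = 0.75, expected rate p1 = 0.85, power 90%, 190 evaluable patients, 200 with 5% attrition. From 2.10: significance level 0.05, sidedness not stated. I assume an upper-tail 0.025 (two-sided 0.05) and an exact binomial test.

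**3. The plan's own figure.** Let X be the number of successes in n = 190. The rule is the smallest r with P(X ≥ r | 190, 0.75) ≤ 0.025.

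- r = 155 (155/190 = 81.6%), exact alpha 0.0197
- Power: P(X ≥ 155 | 190, 0.85) = 0.919
- Attrition: 190/0.95 = 200

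The stated 90% power and 200 patients therefore reproduce. At one-sided 0.05 the rule would be r = 153, with alpha 0.044 and power 0.963.

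**4. Effect of missed failures.** Suppose true success is exactly at the goal, 75%, so that 0.25 × 190 = 47.5 failures are expected. Let m be the proportion of all patients scored as successes only because the tracing was too short. The chance of wrongly meeting the goal is P(X ≥ 155 | 190, 0.75 + m).

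| m | Patients (m × 190) | Share of true failures (m/0.25) | Chance of wrongly meeting the goal |
|---|---|---|---|
| 0 | 0 | 0% | 0.020 |
| 0.01 | 1.9 | 4% | 0.040 |
| 0.02 | 3.8 | 8% | 0.076 |

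The documents give no value for m. These rows are an assumed range, not an estimate. The required sample size does not change.

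**The case against.** Several points on the other side stand.

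- **The short ECG is not in the text.** The article never mentions a 12-lead ECG or a tracing length. The symptom-driven monitoring in 2.5 could be Holter, event recorder or telemetry, all of which can show more than 30 s. Figure 1 was not available for this check and may name the modalities. This limits how often the gap would operate; it does not close it, since 2.7 itself fixes the threshold for every modality.
- **One qualifying recording is enough.** A reader might take the rule to need >30 s in all modalities. It does not. A longer rhythm strip at the same visit, or any later recording over 30 s, makes the patient a failure.
- **Episode or recording.** The duration is attached to the episode, so a centre might accept a tracing filled with AF in a symptomatic patient as part of a longer episode. That is a possible reading, and a reason to settle the wording. There is no evidence that centres would in fact score differently.
- **The benchmark.** The definitions used in the studies behind the 75% goal cannot be checked here. If they used >30 s only, the present rule is the like-for-like one.

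A stronger reading is also tempting. At 85% success, 161.5 successes are expected, 6.5 above the threshold of 155, so a reader might infer that about seven misclassified patients decide the result. The documents do not support this. If true success is 85%, misclassification adds to a result already expected to pass. If instead 161.5 is the observed count, there are 28.5 observed failures, and seven hidden ones would be 7/35.5, about 20% of all true recurrences, appearing only on short tracings. Nothing suggests so large a share. The margin also depends on the assumed alpha: at one-sided 0.05 it is 161.5 − 153 = 8.5.

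**Conclusion.** The point holds in a limited form. As written, 2.7 gives no way for a recording of 30 s or less to count, so a patient whose only post-blanking documentation is a short tracing filled with AF, flutter or atrial tachycardia is a success. This follows from a rule the article states, not from detail left to a fuller document. The direction is towards success.

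The size is unknown and probably small, because the patient must have no longer qualifying recording at any time after blanking. Missing 1 or 2 percentage points of patients would roughly double or quadruple the false-success chance, from 0.020 to 0.040 or 0.076. This rests on n = 190, an exact test at upper-tail 0.025, true success at 75%, and assumed miss rates. Whether the comparison with the literature is itself biased cannot be judged without the benchmark definitions. The wording should be corrected; the documents do not show that it threatens the study's conclusion.

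**What to change.** Amend 2.7 so that a recurrence is AF, atrial flutter or atrial tachycardia after the blanking period that either lasts >30 s on any continuous or event recording, or is present throughout a standard 12-lead ECG. Use the same definition for secondary endpoints 2 to 4, replacing the separate source wording in endpoint 3, and put it in the case report form instructions.

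Report the primary result under the >30 s-only rule as a sensitivity analysis, so that the comparison with the 75% goal can be read under either definition. For this, each recurrence must be recorded with its source and duration.

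The cost is one sentence and the matching form instructions. No extra tests or patients are needed and the sample size is unchanged. The downside is that the observed recurrence rate may be slightly higher, and the amended definition may be stricter than that of the benchmark studies; the sensitivity analysis makes that visible.
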